### Risks

No additional risks for study patients are anticipated, since the application of a circular sterile plastic wound edge protector represents a clinically established standard method. The wound edge protector used in BaFO is CE certified (3 M Steri-Drape Wound Edge Protector, 3 M, St. Paul, MN, USA). All surgical procedures carried out within BaFO are not affected by the trial.

### Outcomes

Primary efficacy endpoint of the BaFO trial is the rate of SSIs according to Center for Disease Control (CDC) criteria, which constitutes the internationally accepted standard definition within 45 days postoperatively [9]. Secondary outcome measure is the intraoperative core body temperature measured at the beginning, in the middle and at the end of the operation via nasal, rectal, transurethral or central venous probes. Temperature as well as the modality of measurement will be recorded.

### Data management

All required information collected during the trial is entered in the case record form (CRF) by the investigator or a designated representative. Documentation is expected to be completed as soon as possible after the information has been collected. The investigator is responsible for the accuracy of the documentation and must ensure that all entries can be verified by source data. An explanation must be given for all missing data. Corrections in the CRF must be signed, dated and leave the corrected entry visible. The completed CRF must be reviewed, signed and dated by the investigator named in the trial protocol or by a designated subinvestigator. After keeping a copy at the trial center, the original CRF is sent in a sealed envelope by certified mail to the Centre for Data Management at the Münchner Studienzentrum (MSZ; member of the Network of Coordinating Centres for Clinical Trials (KKS Network) at the Technische Universität München, Munich, Germany). Double data entry is performed by data management according to standard operating procedures predefined in the data management plan to ensure correct transfer of data from the CRF to the database (hardware: Windows Server NT 2003 (Microsoft, Redmond, WA, USA); software: MACRO™ V.3, Microsoft SQL Database (Microsoft, Redmond, WA, USA); browser: Microsoft Internet Explorer V.6 or higher (Microsoft, Redmond, WA, USA)). Completeness, validity and plausibility of data are examined by validating programs as well as individual inspection and queries are generated accordingly which need to be clarified by the investigator or designated subinvestigator. At the end of the trial the principal investigator will retain the original CRFs.

### Monitoring

Monitoring of the trial data will be performed by an independent institution experienced in the monitoring of surgical trials (KKS Network) at the TUM (Münchner Studienzentrum). Monitoring will be carried out in accordance with ICH-GCP guidelines [44] and standard operating procedures of the MSZ to ensure patients´ safety and integrity of the clinical data, for example, primary outcome measure in adherence to study protocol. All trial sites are activated with an initiation visit by the monitor or CHIR-*Net* coordinator, who will hand out and explain the investigator site file, discuss relevant issues and train trial personnel in study-specific interventions. Regular contact by phone or email with all participating centers will enable the CHIR-*Net* Coordinator and the monitor to control the study progression, adherence to the study protocol, and to discuss problems related to the study. Regular on-site monitoring visits are planned for all sites. Investigators must allow the monitor to look at all essential documents, support the monitor during visits and answer queries. All monitoring procedures will be predefined in a trial-specific monitoring manual. In addition, a GCP-trained flying study nurse employed by the CHIR-*Net* regional center Munich will assist the trial sites with documentation and data collection if needed. Furthermore, close-out visits are planned for each center.

### Safety evaluation and reporting of adverse events

Occurrence of the primary endpoint is assessed as endpoint only (not as adverse event).

The following conditions are expected after the initial operation and will therefore not be classified as adverse events: pain, nausea, vomiting, urinary tract infection, hyper/hypotension, imbalances of blood sugar or electrolytes and other lab values out of range, if they do not exceed grade 3 to 4 in the Common Terminology Criteria for Adverse Events version 3.0 [45]. Assessment will be performed by the investigator or the designated subinvestigator.

From the day the patient has signed informed consent until the regular end of the trial (visit 9) or until premature withdrawal of the patient, all serious adverse events (SAEs) will be documented on a ‘serious adverse events form’ available in the investigator site file. An SAE will be defined as an event, that results in death, is immediately life threatening, requires or prolongs hospitalization or results in persistent or clinically important disability or incapacity as judged by the investigator or designated subinvestigator. SAEs will be classified to intensity (mild, moderate, severe), outcome (ongoing, recovered completely, recovered with sequelae, death, unknown) and causality (unrelated; possibly, probably or definitely related to trial intervention; not assessable). The assessment is based on clinical findings and needs to be performed by the investigator or designated subinvestigator in the participating trial centers. SAEs will have to be reported within 7 days after becoming known.

### Statistical methods

#### Sample size calculation

Sample size calculation is based on the primary end point of surgical site infections within 45 days post operation according to the CDC classification [9] and was conducted by using nQuery Advisor software version 7.0 (Statistical Solutions Ltd, Cork, Ireland). Based on the assumption that the percentage of patients developing postoperative wound infections in a mixed surgical population undergoing midline or transverse laparotomy is approximately 16% for the standard group (control group, see Background) and can be reduced to 8% in the experimental intervention arm, a group sample size of 258 patients would need to be compared by the χ^2^ test, to achieve 80% power in detecting this difference in SSI rate at a 2-sided level of significance of 5%. Analysis of the primary efficacy endpoint will be based on a χ^2^ and not based on a random effects model, which would assume different underlying effects within the centers. However a generalized linear mixed effect model (logit link regression) will be fitted to the data in terms of a supportive sensitivity analysis that allows for assessment of the primary efficacy endpoint under consideration of random center effects. Under the assumption of a dropout rate of up to 15%, a total of 600 patients would need to be enrolled in the study. Due to the broad inclusion criteria, the limited number of exclusion criteria, the limited time frame as well as the comprehensible nature of the trial, no more than 200 patients are expected to be screening failures, which brings the total number of patients that need to be screened for eligibility to 800 (Figure 2).

Based on the multicenter trail design, stratification according to recruiting center will be used [46]. Each participating center will have to enroll a minimum of 15 patients. Centers with fewer than 15 patients will be excluded from the primary efficacy analysis. Therefore, recruitment will be continued until enough centers lead to the required total sample size by each enrolling a sufficient number of patients.

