### Randomization and blinding

Randomization and blinding will be performed with the help of sealed, opaque, individually numbered envelopes, restricted to choosing one at a time. The envelopes contain data sheets with information regarding the group allocation and the randomization number. Both will be prefabricated by a biostatistician of the Technische Universität München (TUM; Munich, Germany). Randomization (visit 2, see Figure 2) will be performed after inclusion of the patient in the trial (informed consent, visit 1) or in the period between inclusion and the trial intervention (day of surgery) or at the day of surgery (visit 3). Randomization will be performed stratified by center. To assure balanced group sizes in the course of the accrual, a blockwise randomization is applied. Basic characteristics of the patient and day of randomization must be documented on the randomization sheets. Subsequently, randomization sheets must be dated, signed and stored away from the patient records, the trial documents and the investigator site file to ensure blinding. Patients, outcome assessors and the trial statistician will be blinded for the trial intervention. The outcome assessor (postoperative SSIs) will therefore neither be part of the surgical team that performs the trial intervention nor have access to the randomization sheets. Patients will be blinded since they are under general anesthesia during the operation and therefore will not be aware which intervention is used during the operation.

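### Randomization is stratified by center but the primary chi-square test leaves center out, and the reason given does not justify that; the cost is mild conservatism, and a stratified test is a free improvement

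*Protocol article*

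**What the plan says.** Under Randomization and blinding, the article states "Randomization will be performed stratified by center" and, to keep the groups balanced during accrual, "a blockwise randomization is applied". The Sample size calculation section repeats that "stratification according to recruiting center will be used", without saying whether this means the design only or also the analysis.

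That section also fixes the primary test as a chi-square and explains that the analysis is "not based on a random effects model, which would assume different underlying effects within the centers". Center enters the analysis through a logit-link mixed model, described as a "supportive sensitivity analysis that allows for assessment of the primary efficacy endpoint under consideration of random center effects". No CMH test and no other center-stratified test with a common effect is mentioned.

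**The concern.** Center is the only stratification factor named, and the primary test does not use it. The rationale treats the choice as one between a pooled test and a random effects model. It passes over the usual option between them: a test stratified by center, which assumes a single treatment effect and allows each center its own baseline risk.

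Baseline risk may well vary. Recruitment and trial timeline describes sites from university to community hospitals, including certified colorectal centers. The Background cites infection rates from 13% to 19% in a mixed abdominal trial and 21% in colorectal controls.

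When allocation is balanced within centers, between-center differences in risk cancel out of the treatment comparison. The pooled chi-square still counts them as noise, so its p-values are a little too large. At stake is a small amount of efficiency, and occasionally a primary result that differs from the center-adjusted one for an avoidable reason.

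**Working it through.** **Inputs from the article.** Control rate "approximately 16% for the standard group"; a rate that "can be reduced to 8% in the experimental intervention arm"; 258 per group; two-sided 5% and 80% power; 0.048 at the final analysis (Analysis section); 15 centers.

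**The plan's own figure.** With pooled rate 0.12, the unstratified two-proportion formula is

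n = [1.960·√(2·0.12·0.88) + 0.8416·√(0.16·0.84 + 0.08·0.92)]² / 0.08²
= (0.9007 + 0.3838)² / 0.0064 = 257.8, so 258.

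This reproduces the stated number exactly (power 80.0% at 0.05, 79.5% at 0.048). The sample size matches the planned unstratified test.

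**Why the pooled test is conservative.** Its variance uses p(1−p). With balance inside centers, the relevant variance is the average of p_c(1−p_c), which equals p(1−p) − Var(p_c). As an example, a center logit SD of 0.6 gives center control rates with an SD of about 8 points. With no treatment effect and p = 0.16:

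- p(1−p) = 0.1344; within-center variance = 0.1344 − 0.08² = 0.1280; ratio 0.952, square root 0.976.
- The critical value for 0.048 is 1.977. The effective value is 1.977 / 0.976 = 2.026, a two-sided level of about 0.043.

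**Simulation.** Assumed: 15 centers with 17 patients per arm (255 per group, close to 258), exact 1:1 allocation within center, normal center intercepts on the logit scale, a common treatment log odds ratio, and marginal rates held at 16% and 8%. There were 40,000 trials per setting; the Monte Carlo standard error of a type I error near 0.046 is √(0.046·0.954/40,000) ≈ 0.001.

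| Center logit SD (assumed) | Type I error at 0.048, pooled chi-square | Power gain of CMH (points) |
|---|---|---|
| 0.4 | not tabulated | about 0.2 |
| 0.6 | about 0.046 (0.044 in a separate run of 20,000) | about 0.8 |
| 0.8 | about 0.040 | about 1.5 |
| 1.0 | about 0.036 (0.038 in the separate run) | about 2.4 |

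CMH type I error was about 0.047 to 0.050. Pooled power stayed at about 80% to 81% throughout. With no center differences the two tests had the same power within simulation error.

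**Unequal centers** (15 to 110 patients, 516 in total, nominal 0.05) give the same picture. Type I error is 4.2% pooled versus 5.0% CMH at SD 0.8, and 3.8% versus 4.9% at SD 1.0. CMH gains 1.3 and 2.1 points of power.

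**The case against.** The case for leaving the plan alone has real weight.

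- **Center is not absent from the plan.** The mixed model with random center effects is prespecified for the primary endpoint. The request is to add CMH and reorder the analyses. This stands.
- **The error is in the safe direction.** The pooled test stays at or below its nominal level. This stands.
- **The heterogeneity is assumed.** The article says that centers differ in type but gives no between-center infection rates. At SD 0.6 or below the gain is under one point. This stands.
- **Discordance is rare.** At SD 0.6 with 16% versus 8%, the pooled and stratified tests reached different verdicts in 0.9% of simulated trials, and keeping supportive analyses leaves some discordance possible anyway. This stands, so discordance is a minor argument.

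Two stronger readings are tempting. First, a reader might call the rationale sentence plainly false. It is not. It speaks of a random effects model, and is true of one with random treatment-by-center effects; it is also true of a random-intercept model if the effects meant are center effects. It is imprecise and does not support omitting center.

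Second, a reader might infer that power falls well below 80%. Holding the conditional odds ratio at (0.08/0.92)/(0.16/0.84) = 0.457 does give pooled power of 77.0%, 75.0% and 73.0% at SD 0.6, 0.8 and 1.0. But the experimental marginal rate then rises to 8.2%, 8.4% and 8.6%, so the effect itself is smaller, and CMH falls too (77.9%, 76.7%, 76.0%). The plan assumes marginal rates of 16% and 8%, at which the planned power is kept.

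**Conclusion.** The point holds as a matter of efficiency and of rationale. The design stratifies by center, the named primary test does not, and rejecting a random effects model is no reason for the omission. The consequence is modest conservatism if centers differ in baseline risk, and up to about 2.4 points of power forgone at the top of the range examined. These sizes rest on an assumed logit SD of 0 to 1.0, a common treatment effect and balance within centers. The documents do not support an inference of inflated false positives, of an underpowered design or of a wrong sample size on this account.

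**What to change.** In the Statistical methods, make the primary test a CMH test stratified by center, reported with a common risk difference or odds ratio and its confidence interval, and use it at both the interim and the final analysis. Keep the pooled chi-square and the prespecified mixed model as supportive. Replace the rationale with a statement that one common treatment effect is assumed while baseline risk may vary by center.

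A logistic model with fixed terms for center and operation type should not be offered as an equivalent. It estimates a conditional odds ratio and adds a factor that was not a randomization stratum. It is also fragile here: about 258·0.16 + 258·0.08 = 62 events are expected over 15 centers, and a center of 15 patients expects 15·0.12 = 1.8 events and has none with probability 0.88¹⁵ ≈ 15%.

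The cost is a few sentences, with no new data and no more patients. Timing matters: the Trial status section reports 323 patients recruited by 29 February 2012, and the interim test follows recruitment and follow-up of 340. The change should be fixed before that look.

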## Background

### Rationale for the trial

Postoperative surgical site infections (SSIs) are one of the most frequent surgical complications and a major cause of postoperative morbidity, prolongation of hospital stay, healthcare costs and even mortality. An estimated 300,000 to 500,000 SSIs occur in the USA annually [1-4]. In Germany SSIs are the third most frequent cause of nosocomial infections and account for approximately 15% of the 400,000 to 600,000 nosocomial infections per year (60,000 to 90,000 cases) according to data from the Robert-Koch Institute (RKI) and the German Nationales Referenzzentrum für Surveillance von Nosokomialen Infektionen (NRZ) [5,6]. Data from the German Krankenhaus Infektions-Surveillance-System (KISS) estimate an even higher number of approximately 128,000 SSIs annually [6]. Furthermore, an estimated 7,500 to 15,000 patients die every year in Germany due to nosocomial infections [7,8].

Despite the implementation of preventive measures such as preoperative antibiotic prophylaxis [9-12] and antiseptic skin cleansing [9,13], SSI rates in prospective trials with adequate follow-up and standardized SSI definition in abdominal surgical patients remain high and vary from 14% to 32% [14-17]. Applying the SSI criteria of the Center for Disease Control (CDC) [9], which differentiate between superficial, deep and organ-space SSIs at postoperative day 30, Darouiche *et al*. reported an overall SSI rate of 16.1% in the control group (povidone-iodine skin preparation) of their randomized controlled trial (RCT) in patients with clean-contaminated abdominal surgery [18]. Seiler et al. reported similar numbers in a randomized multicenter trial comparing three different techniques of abdominal wall closure in abdominal surgical patients with SSI rates varying from 13% to 19% [19]. SSI rates following colorectal surgery seem to be even higher as was shown by Bennett-Guerrero and colleagues, who reported an overall SSI rate of 21% in the control group (and 30% in the intervention group) of their prospective multicenter RCT comparing the application of a gentamicin-collagen sponge versus no intervention in colorectal patients [20]. National data from the USA support these numbers [21].

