#### Analysis

The primary analysis will be conducted according to the intention-to-treat (ITT) principle, that is, all included patients will be analyzed as randomized. Patients with missing primary outcome data will be considered as non-SSI cases if they belong to the control group and as SSI cases if they were randomized to the innovative treatment arm. For purpose of sensitivity analyses, per protocol and complete case analyses of the primary endpoint will be conducted and further appropriate and less conservative missing-value replacement strategies such as multiple conditional imputation [47] will be employed.

A planned interim analysis will be performed after recruitment and follow-up of 340 patients (two-thirds of the planned total). Due to this intended interim analysis, global α error adjustment is performed by the method of O’Brien and Fleming [48]. Therefore, evaluation of the primary efficacy endpoint will be conducted at a 0.005 level of significance (two sided) in the interim analysis and at a 0.048 level of significance (two sided) in the final statistical analysis.

Prespecified subgroup analyses or treatment group comparisons will be performed for: rate of superficial postoperative SSIs (according to CDC classification); rate of deep postoperative SSIs (according to CDC classification); rate of postoperative SSIs of organ space (according to CDC classification); rate of postoperative SSIs (total/superficial/deep/organ space) stratified by the National Nosocomial Infection Surveillance (NNIS) risk score [46]; rate of postoperative SSIs (total/superficial/deep/organ space) stratified by colorectal and non-colorectal operations.

Secondary analyses will be conducted in an explorative manner. Kaplan-Meier analysis and Cox regression analyses will be employed for analyses of time to event endpoints. The χ^2^ test will be used to compare frequency data between intervention groups. As appropriate, the Student t test, Mann–Whitney U test or analysis of covariance (ANCOVA) will be employed for group comparisons of quantitative data. The 95% confidence intervals will be provided for estimates of relevant effect sizes.

Safety analysis includes description and comparison of the frequency of adverse and serious adverse events in the two intervention groups.

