However, wound edge protectors have not yet been rigorously tested in multicenter randomized controlled trials, since the studies available today are either single-center trials, lack clear SSI definitions/endpoints, or only include a small number of patients. Even in the trials available mixed results have been reported. A recent single center trial in elective colorectal patients reported a reduction of SSI rates from 22.7% to 4.7% [30]. Similarly, in a non-randomized single-center prospective trial with 221 patients reported a reduction in SSI rates only for patients undergoing colorectal surgery. Interesting only superficial SSI rates were reduced while rates of organ-space infections remained unchanged [31]. A randomized trial with 352 patients at 2 institutions found a reduction of SSIs from 22.6% to 10.5% with the application of a wound-edge protector in patients with clean/contaminated or contaminated wounds [32]. However, in a report from Psaila *et al*. wound-edge protection did not reduce SSI rate in abdominal surgery [34]. Similarly, a study by Kercher *et al*. reported no benefit of wound protectors in patients undergoing laparoscopic-assisted colon surgery [35], a result that was confirmed for open colorectal surgery by Nyström *et al*. [36]. Furthermore, several of these trials were underpowered. Taken together these conflicting results disallow a definitive answer whether wound-edge protectors constitute a reasonable approach to reduce SSI rates in general and abdominal surgery.

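### No pooled estimate of the primary effect adjusted for type of operation (colorectal or not) is specified; the chi-square test stays valid, but a little precision is given up

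*Protocol article*

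**What the plan says.** Under Sample size calculation, the primary endpoint is to be compared by a chi-square test. The planning rate "is approximately 16% for the standard group (control group, see Background) and can be reduced to 8% in the experimental intervention arm", and "a group sample size of 258 patients would need to be compared by the χ^2^ test". A random-effects model is ruled out as the primary analysis. A generalized linear mixed model with logit link is added as a "supportive sensitivity analysis that allows for assessment of the primary efficacy endpoint under consideration of random center effects"; no patient-level covariate is named.

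Under Randomization and blinding, center is the only stratification factor.

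Under Analysis, SSI rates (total and by depth) are to be reported "stratified by colorectal and non-colorectal operations", and also by NNIS risk score. These appear in the list of subgroup analyses and treatment group comparisons. The final test is made "at a 0.048 level of significance (two sided) in the final statistical analysis".

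On risk by type of operation, Rationale for the trial says "SSI rates following colorectal surgery seem to be even higher". It cites 21% in the control group of a colorectal trial, against 16.1% and 13% to 19% in trials of abdominal surgery. The Discussion cites a single-center colorectal trial with 22.7% before the reduction attributed to the protector, and a non-randomized study that "reported a reduction in SSI rates only for patients undergoing colorectal surgery".

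**The concern.** The trial deliberately enrolls a mixed surgical population. The protocol itself describes one part of that population as having a higher SSI rate and treats the split as important enough for a prespecified subgroup analysis. Yet type of operation is not a randomization stratum, and it does not enter any stated pooled estimate of the protector's effect.

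If one arm happens to receive more colorectal cases, the headline estimate moves with it. Readers would then have that unadjusted figure and two smaller subgroup comparisons, but no single figure that takes case mix into account. Adding the covariate after an imbalance has been seen would be a data-driven choice, which is the reason to fix it in advance.

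**Working it through.** **Inputs from the article.** 258 per group; control 16%, experimental 8%; chi-square; two-sided 5% overall and 0.048 at the final analysis; colorectal control rates of 21% and 22.7%.

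**Assumptions, not in the article.** Colorectal share q from 20% to 60%; overall control rate held at 16%; relative risk 0.5 in both types of operation.

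**1. The plan's own figure.** With pooled variance and no continuity correction, n = [1.96·√(2·0.12·0.88) + 0.8416·√(0.16·0.84 + 0.08·0.92)]² / 0.08² = 257.8, so 258. The stated size is reproduced. Power at 258 is 80.0% at a 5% level and 79.5% at 0.048.

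**2. Non-colorectal rate.** With colorectal rate pc, the other rate is pn = (0.16 − q·pc)/(1 − q), and the contrast is d = pc − pn.
- q = 0.2, pc = 21%: pn = 14.75%, d = 6.25 points.
- q = 0.4, pc = 21%: pn = 12.67%, d = 8.33 points.
- q = 0.6, pc = 22.7%: pn = 5.95%, d = 16.75 points.

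**3. Size of a chance imbalance.** The SD of the between-arm difference in colorectal share is √(2q(1 − q)/258). This is 3.52 points at q = 0.2, 4.31 at q = 0.4 or 0.6, and 4.40 at q = 0.5.

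**4. Shift in the risk difference under a 2-SD imbalance,** 2·SD·d:
- q = 0.2, pc = 21%: 2 × 0.0352 × 0.0625 = 0.44 points.
- q = 0.4, pc = 21%: 2 × 0.0431 × 0.0833 = 0.72 points.
- q = 0.6, pc = 22.7%: 2 × 0.0431 × 0.1675 = 1.44 points.

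The standard error of the planned difference is √[(0.16·0.84 + 0.08·0.92)/258] = 2.84 points. The shift is therefore about 0.16 to 0.51 standard errors, or about 5% to 18% of the 8-point target. This uses the control-arm contrast. If the contrast is averaged over both arms (0.75·d, because the protector halves both rates) and 1.96 SD is used, the range is 0.3 to 1.1 points.

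**5. Power, chi-square against a test stratified by type of operation (Mantel-Haenszel).** The stratified test serves here as a gauge of what adjustment can gain.
- Normal approximation at 5%: 80.0% unadjusted; 80.2% to 81.5% stratified.
- Simulation at 0.048: the change runs from −0.2 to about +1.2 points. For example, 80.5% against 80.3% (q = 0.2, 21%), and 80.5% against 81.6% (q = 0.6, 22.7%).

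**6. Type I error.** At 0.048, simulated rates are about 4.8% to 4.9% unadjusted and 4.7% to 4.9% stratified. Both tests hold their level.

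**7. The unlucky trials.** At q = 0.4 and a 5% level, take only trials with an adverse imbalance above 1.96 SD, about 2.5% of all trials. Power of the unadjusted test falls from 81% to 74% (colorectal rate 21%) or 73% (22.7%). The stratified test stays at about 81%.

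**The case against.** The strongest reply is that nothing here is wrong. Under randomization the unadjusted test is valid, the loss is small, and the covariates of a supportive model are commonly settled in a statistical analysis plan that is not shown. The subgroup analysis already compares the arms within each type of operation. Center-stratified blocks also remove whatever part of the imbalance comes from differences between centers, so the SD in step 3 is an upper estimate. Most of this stands, and it limits the point to a small improvement. It does not supply a pooled adjusted estimate, and the subgroup comparisons are not one.

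A reader might infer more than the document supports:

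- **That the chi-square result would be biased or invalid.** It would not; step 6 shows the error rate is held.
- **That the protocol shows type of operation to drive SSI risk.** It says only that colorectal rates seem higher, and the figures come from different trials with different populations. No contrast within one population is given.
- **That the mixed model contains center and nothing else.** The article describes the model by its purpose and gives no list of terms.
- **That the study with benefit only in colorectal patients calls for adjustment.** It points to effect modification, which a main effect does not address and the planned subgroup analysis does. It was also a non-randomized single-center study.
- **That the primary test should be replaced.** Trial status reports 323 patients recruited and the interim analysis is set at 340. Changing the primary test then would be a substantive amendment for about 0 to 1 point of power.

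**Conclusion.** The point holds as a low-severity improvement. The article commits the primary comparison to an unadjusted test and specifies no pooled estimate adjusted for a variable that it treats as relevant and already plans to use. The cost is precision: about 0 to 1 point of power on average, and a shift of 0.4 to 1.4 points in the risk difference under a 2-SD imbalance. Both ranges rest on the assumed 20% to 60% colorectal share and the 21% to 22.7% colorectal control rates from cited trials. A larger gain, with stratified power up to 84.4%, appears only if the colorectal control rate is set at 30%. That figure comes from the intervention arm of the cited sponge trial and is not a control rate.

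**What to change.** Keep the chi-square test as the primary analysis. Prespecify type of operation (colorectal or non-colorectal) as a fixed effect in the supportive mixed model, alongside the random center effects. Report the adjusted effect, standardized to a risk difference with its confidence interval, beside the chi-square result.

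Use the operation planned before randomization, not the one performed, since the latter can be influenced by events after allocation. The Analysis section does not say which of the two it means, so this should be stated, and it should be confirmed that the planned operation is recorded.

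The cost is about one sentence of analysis text, with no added patients or visits. The small downside is that a logistic model yields a conditional odds ratio, which does not compare directly with the unadjusted result. The standardized risk difference must therefore be reported with it. The wording should be settled before unblinded results are seen.
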